#### Target trial emulation using observational data from TriNetX and CPRD

*Eligibility criteria*. Anonymised, person-level, electronic health data will be extracted from TriNetX and CPRD, linked across primary care, ED, inpatients, outpatients, and mortality subsets. The study period will be from 01/01/2014 to 01/01/2024. Included will be men and women aged 16–54 years. The study will take an open cohort design with patients entering the cohort when the following criteria are met:

Either: ≥1 epilepsy disease or symptom code recorded during the study period and two separate valproate prescription instances over the preceding 12 months before at least one of the epilepsy disease or symptom codes;

Or: ≥1 epilepsy disease or symptom code recorded any time before the study period with at least two separate valproate prescription instances over 12 months during the study period.

TriNetX and CPRD use ICD-10-CM and SNOMED codes, respectively. The coding strategy combining disease and symptom codes with valproate, as used our published study successfully [20], was shown to accurately identify epilepsy cases in our prior work [28,29].

Treatment arms:

Withdrawn valproate and commenced lamotrigineWithdrawn valproate and commenced levetiracetamWithdrawn valproate and no new ASM commencedContinues valproate

*Treatment assignment*. Baseline (time 0) will be defined as when valproate dose reduction commences (treatment arms 1–3) or prescription of valproate at a matched time (arm 4). Eligible individuals are assigned at baseline to the treatment strategy that their data are consistent with [21]. To emulate randomisation, adjustment is made for baseline confounders using Robins’ generalised methods (g-methods, e.g., inverse probability weighting) [21], considering age, sex, ethnicity, deprivation, type of epilepsy (using G40 codes), baseline seizure frequency (symptom codes recorded over preceding 12 months), alcohol excess, developmental delay, Cambridge Multimorbidity Score, length of valproate treatment, valproate dose, and ASMs used other than valproate. The final set of covariates required to adjust for confounding will be chosen using a causal directed acyclic graph [21].

*Outcomes*. These are listed in the target trial design section and derived from our prior work [1,20,30,31], and public consultation. All coded events will be recorded for flexible categorical or continuous analyses, as needed.

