### Addressing Aim 2: Causal prediction modelling

A causal prediction model will be created using Cox-proportional hazards of time-to-first-event in a causal framework [26]. The predicted outcome will be a composite personal harms risk combining epilepsy-related deaths, seizures, injuries, admissions, and depression. Predictors for definite inclusion in the final model will be treatment arms 1–4. Candidate predictors considered in addition will be taken from the list of baseline confounders adjusted in the target trial emulation, alongside any additional variables considered to influence outcome but not treatment assignment. *A priori* clinical expertise and data-driven variable selection will refine the predictor variable list for modelling [30]. Penalisation methods (e.g., *lasso*), will be used to combine variable selection with shrinkage (reducing overfitting risks).

The model will be developed in TriNetX to help ensure it is internationally generalisable [32]. External validation will be undertaken in CPRD, facilitating subsequent clinical implementation [32]. Internal validation within TriNetX will involve 1,000 bootstrap analysis samples. Nagelkerke’s R^2^ and Brier Scores will estimate overall model performance. Calibration will be estimated with calibration-in-the-large, calibration slope, and flexible calibration plots, and discrimination with C-index. Calibration and discrimination will be reassessed within CRPD to externally validate model performance [32]. Counterfactual prediction will be embedded into the model development [26], allowing patients and clinicians to answer clinically meaningful questions such as “at the point of proposed valproate withdrawal, accounting for baseline characteristics, what is the risk of epilepsy-related death or composite morbidity for levetiracetam? And what is it for lamotrigine?”

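### The Aim 2 causal model guarantees a place only to the treatment arms; the confounders are left to selection and shrinkage, and no carry-over of the emulation weights is stated

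*Protocol article*

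**What the plan says.** All references are to the Protocol article.

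- **Aim 1** (Target trial emulation using observational data, Treatment assignment). Baseline confounders are adjusted for by g-methods, with inverse probability weighting as the example. Subject knowledge fixes the set: "The final set of covariates required to adjust for confounding will be chosen using a causal directed acyclic graph".
- **Aim 2, forced terms** (Causal prediction modelling). "Predictors for definite inclusion in the final model will be treatment arms 1–4".
- **Aim 2, optional terms.** "Candidate predictors considered in addition will be taken from the list of baseline confounders adjusted in the target trial emulation", together with further variables thought to affect outcome but not treatment assignment.
- **Aim 2, selection.** A priori "clinical expertise and data-driven variable selection will refine the predictor variable list for modelling". Then: "Penalisation methods (e.g., *lasso*), will be used to combine variable selection with shrinkage (reducing overfitting risks").
- **Aim 2, purpose.** "A causal prediction model will be created using Cox-proportional hazards of time-to-first-event in a causal framework", and "Counterfactual prediction will be embedded into the model development". The worked example asks for a patient's risk on levetiracetam and then on lamotrigine.

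The Aim 2 section names no weights and no g-method. It fixes no rule for choosing the penalty.

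**The concern.** Selecting and shrinking covariates by their contribution to outcome prediction suits a prognostic model. Here the arm terms are to be read counterfactually, as what would happen to the same patient on one drug or another. For that reading the confounders have to be controlled whether or not they earn their place on predictive grounds.

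Lasso-type methods look at a covariate's association with outcome and ignore how strongly it drives treatment choice. A covariate with a large effect on drug choice and a modest effect on outcome is a natural candidate for removal or heavy shrinkage. Because the arms are kept in, they absorb what it leaves behind. Sex illustrates the point: the Introduction reports that regulatory restrictions halved valproate prescriptions in women, so sex plainly influences withdrawal, yet nothing guarantees it a place in the model.

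The planned performance measures are R-squared, Brier score, calibration and C-index. They assess prediction under the treatment each person actually received, so a model with a confounded arm effect can still do well on them. Validation in CPRD reassesses calibration and discrimination, so the same applies. Aim 1 offers no direct cross-check of the drug-against-drug contrast, because its stated estimand compares each of arms 1–3 with arm 4. The output is meant for a public online tool linked from a national decision aid.

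**Working it through.** **1. Reproduce the plan's figure for this model (Table 1).** Inputs: shrinkage S = 0.9, rate 0.068 per year (5,448 / 16,042 / 5 = 0.0679), 5 years, R-squared at 15% of its maximum, P = 20 parameters.

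- Events per person: 0.068 × 5 = 0.34
- lnL0/n = 0.34 × ln(0.068) − 0.34 = −1.254
- Maximum Cox-Snell R² = 1 − exp(2 × −1.254) = 0.9186
- Anticipated R² = 0.15 × 0.9186 = 0.1378
- n = P / [(S − 1) ln(1 − R²/S)] = 20 / [−0.1 × ln(1 − 0.1378/0.9)] = 1,203.6, rounded up to 1,204

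This matches the stated minimum of 1,204.

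**2. Does sample size require the confounders to be optional?** At the same inputs n is about 60.2 per parameter.

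| Parameters | Minimum n |
|---|---|
| 15 (3 arm terms + 12 listed confounders at one parameter each) | 903 |
| 20 (plan) | 1,204 |
| 25 | 1,505 |
| 30 | 1,806 |
| 51 (3 arm terms + 12 confounders + 3 × 12 = 36 interactions) | 3,070 |

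Table 1 cites about 14,234 TriNetX patients, so sample size is no reason to leave the confounders to selection.

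**3. How large could the bias be?** The documents give no confounder strengths, so this step rests on assumptions. In both settings the true hazard ratio (HR) is 1.0, event times are exponential, follow-up is 5 years, the treatment terms are unpenalised, all covariates are open to the lasso, and the model is unweighted.

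- *Moderate setting.* Rate 0.068 per year; two treatment groups of roughly equal size; 19 covariates, 8 of them confounders, each with log-odds 0.15 on treatment and log-HR 0.15 on outcome per SD; 5-fold cross-validation (CV); 100 runs.
- *Strong setting.* Rate 0.083 per year, i.e. −ln(1 − 0.34)/5; two thirds continuing and one ninth in each withdrawn arm; 17 covariates, 6 of them confounders, each with HR 1.13 on outcome and odds ratio 1.8 for levetiracetam v lamotrigine per SD; 10-fold CV; 10 to 40 runs.

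Mean estimated HR:

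| Setting, n | Unadjusted | Confounders forced in | Lasso, CV-minimum | Lasso, one-SE |
|---|---|---|---|---|
| Moderate, 1,204 | 1.17 | 0.99 | 1.03 | 1.17 |
| Moderate, 4,700 | 1.17 | 0.99 | 1.01 | 1.13 |
| Strong, 1,204 | about 1.38–1.46 | 1.02 | 1.16 | 1.50 |
| Strong, 4,000 | as above | 0.98 | 1.03 | 1.42 |
| Strong, 14,234 | as above | 1.00 | 1.03 | 1.31 |

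In the moderate setting at n = 1,204 the one-SE penalty dropped on average 7.5 of the 8 confounders, and the CV-minimum penalty 0.3. At 4,700 the figures were 3.1 and 0. The Monte Carlo SE of log HR there is about 0.01 at 1,204 and 0.005 at 4,700. For comparison, a third of 14,234, the share Table 1 gives as withdrawn, is about 4,745.

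The 1.50 lies at or slightly above the unadjusted value. With few runs and about 1,204 / 9 = 134 people per withdrawn arm, it should be read as roughly no adjustment at all and not as a stable estimate.

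**The case against.** The strongest reply is that the harm depends on the penalised covariates being the model's only control of confounding. A reader might infer that from the section, but the documents do not say it. The model is placed in a causal framework, counterfactual prediction is to be built in, and the Introduction says that the emulation facilitates such models. All of this could mean that the Aim 1 weights are used when the Aim 2 model is fitted. If so, dropping a covariate as a predictor would not by itself reopen confounding. The article is condensed, and the mechanics of weighting and penalty may sit in a fuller document. This stands, and it is why the point is conditional. It does not remove the point, because the article does state a rule on what is certain and what is optional. For a causal model that rule gives the confounders the wrong status unless the weights are present.

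Second, lasso is only an example, and clinical expertise also shapes the list. Both are true. Any method that combines selection with shrinkage raises the same issue, however, and expertise may keep the main confounders without guaranteeing it. That the arms go unpenalised is itself an assumption: the article promises their inclusion and is silent on penalty factors.

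Third, a reader might take a spurious HR near 1.5 as the expected error. The documents do not support that. It needs a one-SE penalty, which the article does not mention, several strong confounders all acting in the same direction, and the minimum sample instead of the cited one.

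Fourth, shrinkage is a deliberate guard against overfitting, and Aim 1 is untouched. Both hold. The remedy keeps shrinkage for the purely prognostic variables.

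**Conclusion.** The point holds in conditional form. The Aim 2 section guarantees the arms and leaves the confounders to data-driven selection and shrinkage, without stating that the emulation weights carry over. Unless they do, residual confounding can enter the comparison of lamotrigine, levetiracetam and no new antiseizure medication, and the planned validation would not show it.

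The documents do not fix the size. Under the assumed strengths, a CV-minimum penalty in samples of 4,700 or more gives an HR of about 1.01 to 1.03 when the truth is 1.0. At the minimum of 1,204 it gives 1.03 to 1.16. A sparse penalty can approach the unadjusted value. What is at stake is bias in the tool's drug ranking, not power. It should be fixed before model development, but it does not undermine the study as a whole.

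**What to change.** In the Aim 2 section, do one of the following:

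1. List the full causal-diagram confounder set, with the treatment arms, as terms certain to be included. Leave both unpenalised, and confine data-driven selection and shrinkage to variables that influence outcome but not treatment assignment.
2. Fit the penalised model in the inverse-probability-weighted population from the emulation, and say so explicitly.

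The cost of the first option is a longer predictor list, less shrinkage and a penalty-factor setting in the software. The 12 listed confounders and 3 arm terms come to 15 parameters only if each confounder takes one. Ethnicity, deprivation, epilepsy type and other antiseizure medications may each need several, as may non-linear age or dose. If the count passes 20, the minimum of 1,204 in Table 1 should be restated, for example as 1,806 for 30 parameters. That remains well within the roughly 14,234 TriNetX patients cited. The second option costs one sentence and reuse of weights that Aim 1 would already have produced, if weighting is the g-method chosen there.

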We recently published a study of 8,991 men and 5,243 women aged 16–54 with epilepsy taking valproate in TriNetX [20]. This was a survival analysis assessing 5-year mortality and morbidity in those withdrawn from valproate between 01/06/2015–01/06/2018 (regardless of whether switched to another ASM), with propensity-matched comparisons to those who remained on valproate. Results suggested substantially increased risks of emergency department (ED) attendances, hospital admissions, falls, injuries, burns and new-onset depression in both men and women withdrawn from valproate [20]. However, these were aggregate data designed to scope potential trends and generate hypotheses, not to probe causal links.

To progress the field, we propose a comprehensive study examining mortality and morbidity outcomes in individuals who either continued valproate, switched to lamotrigine or levetiracetam, or discontinued valproate. Employing a novel approach known as target trial emulation [21,22], this study will replicate a hypothetical randomised-controlled trial (RCT) using person-level retrospective observational data from both TriNetX and Clinical Practice Research Datalink (CPRD, which encompasses 60m UK patients) [23]. Target trial emulation minimises confounder and selection biases in observational studies by statistically emulating randomisation at baseline (time 0) [21]. Individuals are then analysed based on the treatment strategy aligned with their data. Results are available quickly and shown to mirror those of an RCT [21]. This offers a cost-effective and immediate alternative to conducting an RCT [21]; crucial given the urgency for information on valproate withdrawal safety amidst ongoing regulatory changes [24,25]. Additionally, the emulation facilitates creation of causal prediction models [26]. These are developed using observed data alongside causal theory and assumptions to calculate predicted risk under different hypothetical treatment conditions, allowing “what if” questions to be addressed for each potential (counterfactual) outcome [26]. This facilitates actionable prevention [26].

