### Aims

Identify whether there are any differences in mortality or morbidity outcomes between remaining on valproate compared with valproate withdrawal and switch to lamotrigine, levetiracetam, or no new ASM.Develop and validate a causal prediction model that clinicians and patients could use when planning to withdraw from valproate to predict which of these alternative ASMs would have the lowest mortality and morbidity, taking baseline clinical and demographic characteristics into account.

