### Hypotheses

Some morbidity or mortality outcomes will be increased when valproate is withdrawn, regardless of whether switched to lamotrigine, levetiracetam, or no new ASM;The causal prediction model developed will be able to predict which alternative ASMs are safest.

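### The planned validation measures, as normally computed, do not test whether the model's predicted risks under each alternative medicine, or its ranking of them, are right

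*Protocol article*

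**What the plan says.** The target is counterfactual throughout the protocol article. The Introduction says that causal prediction models "calculate predicted risk under different hypothetical treatment conditions". Aim 2 is to "predict which of these alternative ASMs would have the lowest mortality and morbidity, taking baseline clinical and demographic characteristics into account". Hypothesis 2 is that "The causal prediction model developed will be able to predict which alternative ASMs are safest".

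The section on Aim 2 then fixes how performance will be judged. Overall performance comes from Nagelkerke's R² and the Brier score ("Brier Scores will estimate overall model performance"). For the rest, "Calibration will be estimated with calibration-in-the-large, calibration slope, and flexible calibration plots, and discrimination with C-index". Internal validation uses 1,000 bootstrap samples in TriNetX. External validation is in CPRD (spelled CRPD in this sentence): "Calibration and discrimination will be reassessed within CRPD to externally validate model performance".

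Causal reasoning is placed elsewhere: "Counterfactual prediction will be embedded into the model development". No sentence names validation that is weighted, done under each strategy, or aimed at the difference between treatments.

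On model content, only the treatment arms are certain to be included. For everything else, "Candidate predictors considered in addition will be taken from the list of baseline confounders adjusted in the target trial emulation", and these candidates are then narrowed by clinical judgement, data-driven selection and penalisation such as lasso.

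**The concern.** A model can predict well who does badly under usual prescribing and still be wrong about what would happen to a given patient on the other medicine. The listed measures, in their usual form, address the first question. Hypothesis 2 asks the second. If a variable that influences both the choice of medicine and the outcome is missing from the model, the treatment coefficient absorbs its effect. Predictions for people on the treatment they received then stay correct on average, and the between-treatment contrast is biased. Validation in CPRD would not reveal this if prescribing there is confounded in a similar way.

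The section on pathways to impact plans a public online tool, integration into health-system infrastructure and a link from the national valproate decision aid. Good calibration in CPRD would naturally be read as showing that the ranking of medicines has been externally validated.

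**Working it through.** **The plan's own figure.** The article gives no number for validation. Its model-development size does reproduce, though it does not bear on this point. Events per person E = 0.068 × 5 = 0.34. Maximum Cox-Snell R² = 1 − exp{2[E ln(0.068) − E]} = 0.9186, and 15% of that is 0.1378. Then n = 20 / [(0.9 − 1) ln(1 − 0.1378/0.9)] = 1,203.6, which rounds up to the stated 1,204.

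**Exact illustration.** All inputs are assumptions: lamotrigine and levetiracetam groups of equal size; a binary confounder in 45% of the lamotrigine and 15% of the levetiracetam group, so 30% overall; true hazard ratio for levetiracetam against lamotrigine 1.2; baseline 5-year cumulative hazard 0.35, close to the article's 0.34. Risk = 1 − exp(−0.35 × treatment HR × confounder HR).

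With a confounder HR of 2.5, the four cell risks are:
- lamotrigine: 29.5% without the confounder, 58.3% with it
- levetiracetam: 34.3% without, 65.0% with

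A model that omits the confounder fits each arm's observed average:
- levetiracetam: 0.85 × 34.3 + 0.15 × 65.0 = 38.9%
- lamotrigine: 0.55 × 29.5 + 0.45 × 58.3 = 42.5%

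In new patients treated in the same way, observed/expected (O/E) is 1.00 in each arm by construction. The true risks, if everyone took the medicine in question, use the overall prevalence:
- levetiracetam: 0.70 × 34.3 + 0.30 × 65.0 = 43.5%
- lamotrigine: 0.70 × 29.5 + 0.30 × 58.3 = 38.2%

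The ranking is reversed. Validation weighted on the confounder would show O/E of 43.5/38.9 = 1.12 and 38.2/42.5 = 0.90.

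The same calculation over a range (levetiracetam minus lamotrigine, percentage points):

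| Confounder HR | Model difference | True difference | Weighted O/E (lev, lam) |
|---|---|---|---|
| 1.0 | +4.8 | +4.8 | 1.00, 1.00 |
| 1.3 | +2.8 | +5.0 | 1.03, 0.97 |
| 1.5 | +1.5 | +5.1 | 1.05, 0.95 |
| 1.7 | +0.4 | +5.2 | 1.07, 0.94 |
| 2.0 | −1.2 | +5.3 | 1.09, 0.92 |
| 2.5 | −3.6 | +5.3 | 1.12, 0.90 |

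Unweighted arm-level O/E is 1.00 in every row. Baseline hazards of 0.25 and 0.30 give the same pattern.

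**Can the listed measures favour the wrong model?** A Cox simulation used stronger assumed confounding: 600,000 development and 600,000 validation records, true HR 1.25, confounder HR 1/3, confounder-treatment odds ratio 7.4, confounder omitted.

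| | Model as fitted | Same predictors, HR set to the true 1.25 |
|---|---|---|
| HR used | 0.77 | 1.25 |
| O/E by arm (lev, lam) | 0.993, 0.996 | 0.81, 1.24 |
| Calibration slope | 0.999 | 0.86 |
| C-index | 0.634 | 0.618 |
| Brier score | 0.1393 | 0.1409 |

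The fitted model predicts 15.9% for levetiracetam and 19.9% for lamotrigine. The truth is 19.8% and 16.4%. In this setting the unweighted measures prefer the model with the wrong ranking.

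**Limit of weighting.** In a smaller run (40,000 records) with the same hazard and odds ratios, weights that included the confounder gave O/E of 1.22 and 0.88 and exposed the error. Weights without it gave 0.97 and 1.06 and did not.

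**The case against.** The strongest reply is that the article never says validation will be unweighted. Brier score, calibration and C-index can each be computed under a strategy with weights, the model is set in a causal framework, and a condensed article may leave weighting to a fuller plan. It is right that the text does not commit to factual validation. A reader might infer that it does, but the documents support only this: the measures are listed in standard form, and counterfactual work is tied to development. The point still stands because the article settles which measures and which dataset will judge the model, and none of them, as listed, addresses the treatment contrast that Hypothesis 2 asserts.

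A reader might also infer that the ranking will come out reversed, or that lasso will remove a strong confounder. Neither follows. In a check at n = 1,204 with 20 candidate parameters (logistic approximation, 20 runs per setting), cross-validated L1 selection dropped the confounder in 0 of 20 runs at HR 1.7, 2.0 and 2.5, and in about 5 to 15% of runs at HR 1.3 to 1.5. At those weaker values omission shrinks the contrast but does not reverse it. TriNetX is expected to supply about 14,234 people, which makes loss of a strong confounder less likely still. Clinical judgement also enters the selection.

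Two further limits stand. The documents give no evidence that confounding in CPRD runs in the same direction as in TriNetX; that is an assumption. And near-exact agreement applies to calibration only: the C-index of 0.634 is unremarkable, and simply does not show the error.

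Aim 1 offers only partial cover. It adjusts with a confounder set chosen by causal diagram, but its stated estimand compares arms 1 to 3 with arm 4, names no lamotrigine-levetiracetam contrast, and does not test the model's individual rankings.

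**Conclusion.** The concern holds in limited form. The measures listed, computed in the usual way, cannot support Hypothesis 2, however good their values in TriNetX or CPRD. Calibration can be exact overall and by arm while the treatment contrast is wrong.

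Under the illustrative inputs, a true difference of about 5 percentage points shrinks to between 2.8 and 0.4 points at confounder HRs of 1.3 to 1.7, and changes sign from about 2.0. Without an omitted confounder there is no such error. The size therefore rests on assumed prevalence, effect sizes and omission, none of which the documents supply. A reversed ranking is a possibility that the plan would not detect, not a forecast. An attenuated contrast is the more plausible result of variable selection.

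**What to change.** 1. Keep the Aim 1 confounder set chosen by the causal diagram in the prediction model, or in the weights used to fit it, whatever lasso selects.
2. In the TriNetX bootstrap and in CPRD, also report calibration, Brier score and C-index under each of the four strategies. Use people following that strategy, weighted by the inverse probability of treatment and of censoring for deviation, with the full confounder set in the weights.
3. Compare predicted with weighted observed lamotrigine-levetiracetam risk differences across groups of predicted benefit. Arm-level O/E moves only a few per cent at modest confounding (1.03 and 0.97 at HR 1.3), so this direct check of the contrast is needed as well.
4. Base the conclusion on Hypothesis 2 on items 2 and 3, and report the usual measures as performance under current prescribing.
5. State that the weighted checks detect only measured confounding, and add a sensitivity analysis for unmeasured confounding.

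The cost is more analysis and wider intervals for the performance measures. No new data are needed, and the Aim 1 confounder set and weights can be reused.
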